**Methods:**

The aim of this two-arm open-label randomized controlled trial is to examine the effectiveness of an online, self-guided integrated treatment for problem gambling and tobacco smoking. A target sample of 214 participants will be recruited and be randomized into either an 8-week integrated or gambling only control condition. Both conditions will consist of seven online modules following cognitive behavioural therapy and motivational interviewing principles. Our three primary outcomes are (1) the number of days gambled, (2) money spent on gambling activities, and (3) time spent in gambling activities. Secondary outcomes include gambling disorder symptoms, cigarette use, and nicotine dependence symptoms. Assessments will be completed at baseline, at completion (i.e. 8 weeks from baseline), and at follow-up (i.e. 24 weeks from baseline). Generalized linear mixed modelling will be used to evaluate our primary and secondary outcomes. We expect that participants receiving online integrated treatment will show larger reductions in gambling relative to those receiving a control gambling only intervention. We further hypothesize that reductions in smoking will mediate these group differences.

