## Methods/design

### Design

This open-label pilot project will consist of a two-arm RCT (Clinicaltrials.gov ID NCT03614884; see Figs. 1 and 2 for an overview). [name] and his research team will collect the data in Canada and the USA. Participants will be randomly assigned into one of two conditions. In the experimental condition, participants will receive an 8-week online integrated intervention for problem gambling and smoking. In the control condition, participants will receive a similar 8-week online intervention for problem gambling without treatment content to address smoking. Online assessments will occur before randomization (T0; baseline), at 8 weeks since baseline (T1; treatment end), and at 24 weeks since baseline (T2; follow-up; see Table 1). The timeline of these assessments, including the longer-term follow-up, is consistent with previous RCTs examining technology-based interventions for problem gambling and those for smoking cessation [62, 63]. Participants will be compensated based on the following schedule: $20 per assessment, a bonus of $20 for completing all three assessments, and $20 for completing at least five of the treatment modules (max compensation per participant = $100). For ethical reasons, participants will be compensated in the form of gift cards to Amazon.ca. This RCT is registered with ClinicalTrials.gov for transparency and to avoid publication bias. Prior to the initiation of the study, we obtained ethical approval from the Research Ethics Board (REB) at the University of Manitoba (#P2018:088 HS22037) and York University (ES2020-006).

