### Sample-size justification and statistical plan

A meta-analysis showed that CBT/MI (relative to control) treatments have medium effects on gambling [17]. However, we will be comparing two active treatments, which may result in smaller effect sizes. Accordingly, we used G*Power to calculate the sample size needed to detect a small effect size for our primary outcome. We used a 2 (between subjects; treatment condition) by 3 (within subjects; time) mixed design. Assuming a power rate of .80, an *α* of .05, and a correlation of .50 between repeated measures, the required sample size to detect a small effect size is *N* = 164. Given an average attrition rate of 30% in gambling treatment studies [17], our final adjusted sample size is *N* = 214. Generalized mixed modelling will be used to evaluate the main hypothesis that integrated online treatment will result in the larger reductions in gambling than the gambling only treatment. Primary and secondary outcomes will be tested sequentially. We will include all randomized participants in analyses (i.e. intent-to-treat). Missing data will be accounted for using full information maximum likelihood estimation. We will include some covariates in our models if needed. Relevant covariates may include history of psychological treatment, age, gender, and baseline severity of gaming and smoking behaviours. Of particular relevance, we expect variability in adherence to NRT; therefore, we will explore whether NRT use (e.g., # of days patch was used during treatment) affects primary/secondary treatment outcomes.

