#### Primary outcomes

##### Gambling behaviour

There will be three primary outcomes to capture intervention-related change in gambling behaviour. Specifically, participants will be asked about their past-30-day gambling frequency (# of days gambled), money spent on gambling activities (in dollars), and time spent engaged in gambling activities (# of minutes). These primary indices were selected because they are common outcomes in RCT studies examining CBT/MI approaches to the treatment of problem gambling [17, 70]. The Timeline Followback (TLFB) procedure will be used to collect data for the primary outcomes [71]. Anchoring gambling to specific calendar dates helps to improve the accuracy of self-reported involvement in these activities. The TLFB procedure has also been shown to produce relatively accurate estimates of addictive behaviour involvement when participants are ensured anonymity [72]. Furthermore, recent data shows that a self-report web-delivered version of the TLFB (like the one to be used in this study) produces reliable and valid estimates of addictive behaviours [73].

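### Three unranked primary outcomes, a sample size for one of them at the full .05, and a sequential-testing rule with no order or stopping condition

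*Protocol article*

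**What the plan says.** The Abstract (Methods) lists the primaries: "Our three primary outcomes are (1) the number of days gambled, (2) money spent on gambling activities, and (3) time spent in gambling activities". The Primary outcomes section repeats the number: "There will be three primary outcomes to capture intervention-related change in gambling behaviour". Neither place ranks them or states a success criterion.

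The section Sample-size justification and statistical plan describes one calculation, made to "calculate the sample size needed to detect a small effect size for our primary outcome", with the outcome in the singular. The design is given as "We used a 2 (between subjects; treatment condition) by 3 (within subjects; time) mixed design", with power .80, alpha .05 and "a correlation of .50 between repeated measures". The result is N = 164, raised to 214 for attrition. The main hypothesis in that section is a larger reduction in gambling under the integrated treatment. It is not tied to one of the three measures.

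The same section's only rule for multiple tests is "Primary and secondary outcomes will be tested sequentially". The Design section sets the post-baseline assessments "at 8 weeks since baseline (T1; treatment end), and at 24 weeks since baseline (T2; follow-up; see Table 1" and does not make either one primary.

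**The concern.** Sequential testing controls the family-wise error only if the order is fixed in advance and testing stops at the first non-significant result. The protocol states neither. Its sentence can be read in three ways:

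- a gated fixed sequence;
- one test after another, with no gate;
- primaries as a block first, then secondaries.

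The third reading is natural, because the sentence names primaries and secondaries together, and it gives no protection among the three primaries.

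At stake is the main claim. With the rule open, the analyst could report the integrated arm as better on whichever of days, money or time reached .05. Participants know their arm and the outcomes are self-reported, so the result already carries some risk of bias, and an open success rule adds to it. The sample size also matches only one of the possible rules.

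**Working it through.** **1. Reproduce the plan's figure.** Inputs from the statistical plan section: k = 2 groups, m = 3 times, correlation ρ = .50, α = .05, power .80. Assumption: a small effect means Cohen's f = 0.10, since the protocol gives no number.

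For the within-between interaction, as G*Power computes it:

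- λ = f²·N·m/(1 − ρ) = 0.01 × 164 × 3 / 0.50 = 9.84
- df1 = (k − 1)(m − 1) = 2
- df2 = (N − k)(m − 1) = 162 × 2 = 324
- critical F at .05 = 3.024
- power from the noncentral F = .805 at N = 164, and .7998 at N = 162

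The smallest even N is therefore 164, as stated. The between-groups variant would need 526. So 164 belongs to one 2-df group-by-time test, for one outcome, at the full .05.

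**2. Error with three ungated tests.** If the tests are independent, the two-sided rate is 1 − .95³ = .143, and the rate in favour of the integrated arm is 1 − .975³ = .073. For correlated outcomes I used simulation under the global null (2,000,000 draws, equal correlation r among the three). The documents give no correlations, so a range is shown.

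| r between outcomes | at least one of three, two-sided | at least one favouring the integrated arm |
|---|---|---|
| 0 | 14.3% | 7.3% |
| .3 | 13.6% | 6.8% |
| .5 | 12.5% | 6.2% |
| .7 | 11.0% | 5.5% |
| .8 | 9.8% | 4.9% |
| .9 | 8.4% | 4.2% |

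A single two-sided test at .05 gives 5% and 2.5%. Using the 2-df group-by-time test for each outcome changes little: 12.7% at r = .5, 11.2% at r = .7 and 8.5% at r = .9. The directional column applies to single-contrast tests, because the 2-df test has no direction of its own.

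**3. Error under the other readings.** A fixed sequence with stopping gives 5.0%, because under the global null an error needs the first test to fail. Requiring all three outcomes to succeed gives less than 5% (2.3% even at r = .9).

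**4. Power if alpha is split.** The first Holm step uses .05/3 = .0167, with a critical F of 4.147. Power at N = 164 falls from .805 to .665. Reaching .80 at that level takes N = 212 before attrition.

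**5. Does the calculation carry over to a single contrast?** Take group differences δ in standard-deviation units with f = 0.10 and N = 164. The interaction f² is the variance of the three differences divided by 4. With ρ = .50, the change from T0 to T2 has variance 2(1 − .50) = 1.

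- Sustained pattern (0, δ, δ): f² = δ²/18, so δ = .424. Power for T2 alone is .77.
- Linear pattern (0, δ/2, δ): f² = δ²/24, so δ = .490. Power for T2 alone is .88.
- Effect halved by T2 (0, δ, δ/2): δ = .490. Power for T2 alone is .34.

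The .80 belongs to the interaction test and does not transfer to a single time point.

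**The case against.** The sentence does allow a proper fixed sequence. The outcomes are numbered (1) to (3) in the Abstract and listed in the same order under Primary outcomes, and on that reading the error is 5%. A condensed article may also leave order and gate to an analysis plan that is not shown. The study is called a pilot throughout, with larger trials to follow. These points stand, and they lower the severity. They do not remove the problem, because the article itself states an alpha, a sample size for one primary outcome, three primaries and a testing rule, and these do not fit together. The numbering is nowhere called a testing order.

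Three stronger readings are tempting, and the documents do not support them:

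- A reader might infer that each outcome is powered and tested separately at T1 and T2. Six ungated tests would give about 15% to 25% (r = .9 to 0, with the two change contrasts correlated .5). But the protocol describes one calculation, for a test that spans all three times, and no separate tests at each time.
- A reader might infer that a win on any one outcome suffices. The protocol does not say so; it leaves the criterion open.
- A reader might take 11% to 14% as the chance of wrongly declaring the integrated arm better. Those figures count both directions and need correlations no higher than about .7. All three measures come from the same 30-day calendar procedure, so higher correlations are possible.

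It is also fair to say that no alpha split is needed under a fixed sequence, and that Holm's power per outcome is at least its first-step power. The Recruitment section gives a target of 300; 70% of that is 210, where power at .05/3 would be .797. That target conflicts with 214, so it cannot be relied on here.

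**Conclusion.** The point holds in limited form: the stated alpha, the sample size and the testing rule do not match, and the rule as worded does not protect the error rate among the three primaries. The excess error is conditional. It is about 8% to 14% two-sided, or 4% to 7% in favour of the integrated arm, only if there is no gate and any one outcome counts as success. If the sentence means a fixed sequence with stopping, there is no excess. The figures assume f = 0.10, equal allocation and equally correlated outcomes with r from .9 to 0. Severity: should be fixed. The trial tests a powered, directional hypothesis, so the pilot label does not excuse an open rule, but a short clarification settles it.

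**What to change.** Amend the section Sample-size justification and statistical plan before outcome data are analysed.

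**Preferred.** Test the group-by-time interaction for the three primaries as a fixed sequence in the order already listed (days, then money, then time), each at .05, stopping at the first p > .05. Test secondaries only after all three succeed, or label them exploratory. The existing calculation (.05, N = 164) then holds for the first outcome. The cost is that money and time can be claimed only if the outcomes before them succeed.

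**Alternative.** Use Holm at a family-wise .05 and restate first-step power at .05/3: about .67 at N = 164 with f = 0.10. The cost is the lower stated power, or a larger sample (212 before attrition for .80).

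**If one time point or an averaged contrast is made primary instead,** restate the power for that contrast and for the assumed course of the effect.

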### Integrated treatment (experimental condition)

Participants in this condition will have access to seven treatment modules over 8 weeks (see Fig. 3 for the overview of the module interface). The specific gambling content will be adapted from a self-help intervention developed by [name] (a co-investigator on the proposed project; see Table 2 for module content for integrated intervention). This intervention has been validated in several trials [38, 70] and has been successfully adapted for online delivery [55, 80]. Smoking content will be adapted from existing evidence-based CBT/MI protocols, including the most widely used best practice guidelines from both Abrams et al. and Fiore and colleagues [55, 81]. One standard care guideline for smoking cessation interventions is the combined use of nicotine replacement therapy (NRT) and psychosocial support (CBT/MI) [55, 81]. Accordingly, in the first module, participants in the integrated treatment arm will be provided with an extensive fact sheet on NRT use—including the strong evidence supporting its use in conjunction with psychosocial treatment for smoking cessation. Participants will be (1) encouraged to use NRT patches for the 8 weeks of active treatment, (2) advised that NRT patches are available over the counter at any local pharmacy, (3) provided with NRT patches for the duration of treatment, and (4) advised to consult with their family physician should they have any medical questions related to NRT patches. As noted in best practice guidelines [81], the dosage schedule of NRT patches will be the following: 24 mg for 4 weeks then 14 mg for 2 weeks and finally 7 mg for the remaining 2 weeks. NRT will be mailed out to each participant at the outset of their registration to ensure that they have it for the duration of the pilot study. NRT usage will be tracked weekly during the active intervention and also at each follow-up assessment.

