### Gambling only treatment (control condition)

The control group will receive a similar 8-week online intervention for gambling only. The gambling content will be the same as in the experimental condition, but there will be no treatment content about smoking and no integrated content. The complete module content for the gambling only (control) arm is summarized in Table 3.

**Table 3 Tab3:** Module content for gambling only (control) intervention

Module number and title	Module content
M1: Introduction	• Introduction to the intervention and website
	• Motivational enhancement (i.e. identifying reasons for change, and pros and cons of gambling and not gambling)
	• Self-monitoring gambling behaviours
M2: Goal setting	• Determine personal goals related to gambling (i.e. abstinence versus harm reduction)
	• Develop SMART (specific, measurable, achievable, realistic, and timely) goals for gambling reduction
M3: Risk situations	• Resisting gambling in specific situations (e.g. situations involving negative emotions)
	• Developing personal strategies to reduce/abstain from harmful gambling and to control access to money
	• Introduce need for pleasurable activity scheduling (i.e. behavioural activation)
	• SMART goal setting for pleasurable, low-risk, and healthy activities (e.g. activities that are incompatible with gambling)
M4: Cravings	• Psychoeducation about craving
	• Introduce self-monitoring of craving
	• New ways to effectively cope with cravings (e.g. distraction, urge surfing, and recalling the negative outcomes of gambling)
M5: Unhelpful thinking	• Review common thinking errors related to gambling (or “gambling traps”)
	• Psychoeducation about games of chance
	• Identify how misperceptions about gambling odds impact one’s inner dialogue or thoughts
	• Introduce the thought record as a way to see associations between situations, automatic thoughts, behaviours, and gambling consequences
	• Help foster identification of “gambling traps” and strategies to challenge them
M6: Dealing with slips	• Define a “slip” versus a full-blown relapse
	• Introduce ways to cope with slip in gambling
	• Introduce relapse prevention planning
M7: Preserve your success	• Identify “early warning signs” for slip/relapse
	• Create personalized relapse prevention plan
	• Discuss ways to cope with relapse
	• Identify top five coping strategies for preventing gambling
	• How to know if more treatment is needed (with corresponding recommendations)

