### Ethical considerations

The intervention will be designed to adhere to the ethical principles of the Declaration of Helsinki. Ethics approval will be obtained from the REB at the University of Manitoba and York University before study initiation. Participant data will be kept confidential. To achieve this, we will be using arbitrary identifiers (e.g. numerical IDs) for participants. These identifiers will be used to link data over time, but the data set will not contain personal information. We will keep a master list of participant contact information in a separate password-protected master list. We are also aware of the increased risks associated with recruiting adults with clinically elevated gambling problems, considering the high rates of comorbid mental health problems with disordered gambling [86]. We would expect higher base rates of suicidality and self-harming behaviours in these individuals relative to those without these substance use and behavioural addiction concerns. Accordingly, we will have safeguards to minimize risk of harm. Adults who report significant suicide ideation and/or plans during screening will be given a recommendation to visit their local medical professional (GP or hospital) for support. They will also be given access to the integrated intervention, but their data will not be analysed. We will also be monitoring changes in suicidality at each assessment and will direct participants to emergency services if needed. Participants will also have full-time access to a list of mental health services listed on the intervention website, including community resources, public and private psychologists, hospitals, and helplines. [name] will be available to speak with participants if serious issues arise (i.e. increase in suicidal ideation) and will make sure a safe course of action is followed. The reporting of harms is the responsibility of [name] as outlined in the approved ethics documents. If a participant feels uncomfortable at any time during treatment, they are free to withdraw and cease their involvement in the trial. For ethical reasons, people with clinically elevated AUD/SUD symptoms will be provided with access to the integrated treatment instead of being denied access should they require the intervention as a resource for their problem gambling and/or smoking behaviours. However, their data will not be included in the study. Finally, participants in the gambling only control condition will be given access to the active integrated treatment after the final assessment (6 months) should they wish. They will receive all elements of the integrated arm, including NRT.

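### Baseline adjustment is left to an undefined need; fixing it in advance would be worth 33% to 50% more participants at the protocol's own correlation, unless the model already constrains baseline means

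*Protocol article*

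**What the plan says.** All of the analysis wording is in the protocol article, section Sample-size justification and statistical plan.

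- The design used for sizing: "We used a 2 (between subjects; treatment condition) by 3 (within subjects; time) mixed design". Design and Table 1 show that the three times are T0 (before randomisation), T1 (8 weeks) and T2 (24 weeks), so baseline is one of the repeated outcomes.
- The sizing inputs: "Assuming a power rate of .80, an *α* of .05, and a correlation of .50 between repeated measures", a small effect without a number, and N = 164, raised to 214 for 30% attrition.
- The model: a generalized mixed model on all randomised participants, with full information maximum likelihood for missing data. No contrast is named, and nothing is said on how the T0 means are treated.
- The covariate rule: "We will include some covariates in our models if needed", followed by "Relevant covariates may include history of psychological treatment, age, gender, and baseline severity of gaming and smoking behaviours".
- A separate sentence on nicotine replacement therapy (NRT): "we will explore whether NRT use (e.g., # of days patch was used during treatment) affects primary/secondary treatment outcomes".

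Elsewhere, integrated-arm participants are "provided with NRT patches for the duration of treatment" (Integrated treatment). For controls, "there will be no treatment content about smoking and no integrated content" (Gambling only treatment). Controls are offered the integrated programme after the final assessment: "They will receive all elements of the integrated arm, including NRT" (Ethical considerations).

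**The concern.** The article states a rule, and the rule is discretionary. Whether to adjust, and for what, can be decided after the data are seen. Five candidates are named (treatment history, age, gender, baseline gambling-type severity, baseline smoking severity). Each can be in or out, which gives 2^5 = 32 possible models per outcome and 3 × 32 = 96 across the three primary outcomes, and the list is open-ended. These models would give correlated answers, but a reader of the results could not tell how one was picked.

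Precision is also at stake. Each primary outcome is measured at T0 and predicts its own later values. A mixed model that carries T0 as an outcome with free means in each arm estimates the treatment effect as a difference in change from baseline. That is less efficient than adjusting for baseline.

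A smaller matter concerns patch-days. They arise after randomisation, are trial-supplied to one arm, and form part of the treatment. They also lie on the pathway of the second aim, that reduced smoking explains the gambling benefit. If they entered a model alongside arm, the arm coefficient would no longer be the randomised comparison. The text does not say that they will enter, and does not say that they will be kept out.

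**Working it through.** **Inputs.** From the protocol: α = .05, power .80, ρ = .50, three times including T0, N = 164 before and 214 after attrition, 30% attrition. Assumed: f = 0.10 for the small effect, equal variances σ² and equal correlations across times, approximately continuous outcomes, equal arms.

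**1. The plan's own figure.** For the group-by-time interaction, λ = f²·N·m/(1 − ρ) = 0.01 × 164 × 3 / 0.50 = 9.84, with 2 and 2(N − 2) df. Power is 0.805, and 164 is the smallest even N reaching .80. The between-subjects version of the calculation would need 526. So 164 was sized on the interaction, with T0 as one of the outcomes.

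**2. Variance per participant of the treatment contrast, ρ = .50, in units of σ².**

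Average of T1 and T2:
- follow-up only: (1 + ρ)/2 = 0.75
- change from T0: (1 + ρ)/2 + 1 − 2ρ = 0.75
- adjusted for T0: (1 + ρ)/2 − ρ² = 0.75 − 0.25 = 0.50
- ratio 0.75/0.50 = 1.50, so 164 adjusted matches 164 × 1.50 = 246 unadjusted

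Single time point:
- follow-up only: 1.00
- change from T0: 2 − 2ρ = 1.00
- adjusted: 1 − ρ² = 0.75
- ratio 1.33, so 164 adjusted matches about 219 unadjusted

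At ρ = .50 the follow-up-only and change comparisons have the same variance, so the gain is the same against either. A simulation of 4,000 trials of 164 gave ratios of 1.505 and 1.504 for the averaged contrast.

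**3. Range over ρ, averaged contrast.**

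| ρ | follow-up only | change | adjusted | ratio vs follow-up only | ratio vs change |
|---|---|---|---|---|---|
| .3 | 0.65 | 1.05 | 0.56 | 1.16 | 1.88 |
| .5 | 0.75 | 0.75 | 0.50 | 1.50 | 1.50 |
| .7 | 0.85 | 0.45 | 0.36 | 2.36 | 1.25 |
| .8 | 0.90 | 0.30 | 0.26 | 3.46 | 1.15 |

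Adjustment has the smallest variance in every row.

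**4. Detectable difference.** Analysed: 214 × 0.70 = 149.8, about 150. For a 1-df averaged contrast at 80% power, the detectable difference is 2.80 × √(4V/N).
- V = 0.75: 2.80 × √(3/150) = 0.396 SD
- V = 0.50: 2.80 × √(2/150) = 0.323 SD

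Both use the same 1-df test, so the difference is due to baseline adjustment alone. The Recruitment section gives a target of 300. That would lower both figures but leave the ratio unchanged.

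**5. Where baseline enters matters.** With complete data and equal correlations, adding baseline severity as a main effect while T0 stays among the outcomes with free means does not change the group-by-time contrast, because a between-subject covariate does not affect a within-subject comparison. So the listed covariate, even if included, need not deliver the gain in step 2.

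**6. NRT passages side by side.** The covariate list contains only pre-randomisation items and ends before NRT. The next sentence opens by marking NRT as particularly relevant and uses the verb explore. It covers both primary and secondary outcomes and does not say whether the exploration is within the integrated arm or pools the arms.

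**The case against.** **The detail may be in an SAP.** The exact covariates and the handling of baseline commonly sit there, and none is shown. That is fair for detail that the article merely leaves out, and nothing here rests on the lack of a list. What remains is that the article does state a rule and makes it conditional on an undefined need. An SAP that fixed the covariates would have to replace it.

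**Baseline is already in the model.** This is true, since T0 is a repeated outcome. If the model constrains T0 means to be equal across arms, the gain is already taken. The article neither says this nor rules it out.

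**The 50% is conditional.** This stands. It needs ρ = .50 and a contrast over both follow-ups. Days, dollars and minutes in a generalized model need not follow these variance formulas, so the figures are a guide.

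**Stronger readings that the documents do not support.**
- A reader might infer that patch-days are on the covariate list. They are not, and the exploratory sentence is compatible with an analysis inside the integrated arm.
- A reader might want a size for the bias from conditioning on patch-days. The documents give no figures on patch use or its link with motivation or outcome, so any size would be an artefact of chosen inputs. Control patch-days cannot be taken as exactly zero either, since the article notes that patches are sold over the counter.
- A reader might compare the planned 2-df interaction with a baseline-adjusted 1-df contrast and credit the whole gain to adjustment. Part of it comes from naming a single contrast, which is a different matter from covariates.

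**Conclusion.** The point holds as an improvement that costs nothing. It does not show that the planned analysis is invalid. The stated covariate rule leaves adjustment, including for baseline, to be settled with data in hand, in an open-label trial with three primary outcomes. A fixed baseline adjustment removes that choice and is worth 50% more participants on the averaged contrast or 33% at one time point, under the protocol's ρ and approximately continuous outcomes. It is worth nothing further if T0 means are already constrained equal.

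The NRT wording supports only a clarification. The text leaves open, but does not plan, the entry of a post-randomisation variable into the arm comparison.

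**What to change.** 1. Replace the conditional covariate sentence with a fixed rule: every outcome model adjusts for the baseline value of its own outcome. Either T0 is a covariate with T1 and T2 as the outcomes, or T0 stays in the outcome vector with its means constrained equal across arms. The second form keeps everyone with a T0 value in the likelihood, which suits the stated intent-to-treat and maximum-likelihood approach.
2. Name any further baseline covariates before analysis. The candidates listed are already collected at T0.
3. Add one sentence: NRT use will not enter the treatment-effect models, and will be explored separately within the integrated arm and labelled observational.

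The cost is wording before analysis, with no new data. The downside is that the freedom to choose covariates later is given up.
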